## Abstract

**Background:**

The aim of this trial is to evaluate the effect of SENATOR software on incident, adverse drug reactions (ADRs) in older, multimorbid, hospitalized patients. The SENATOR software produces a report designed to optimize older patients’ current prescriptions by applying the published STOPP and START criteria, highlighting drug-drug and drug-disease interactions and providing non-pharmacological recommendations aimed at reducing the risk of incident delirium.

**Methods:**

We will conduct a multinational, pragmatic, parallel arm Prospective Randomized Open-label, Blinded Endpoint (PROBE) controlled trial. Patients with acute illnesses are screened for recruitment within 48 h of arrival to hospital and enrolled if they meet the relevant entry criteria. Participants’ medical history, current prescriptions, select laboratory tests, electrocardiogram, cognitive status and functional status are collected and entered into a dedicated trial database. Patients are individually randomized with equal allocation ratio. Randomization is stratified by site and medical versus surgical admission, and uses random block sizes. Patients randomized to either arm receive standard routine pharmaceutical clinical care as it exists in each site. Additionally, in the intervention arm an individualized SENATOR-generated medication advice report based on the participant’s clinical and medication data is placed in their medical record and a senior medical staff member is requested to review it and adopt any of its recommendations that they judge appropriate. The trial’s primary outcome is the proportion of patients experiencing at least one adjudicated probable or certain, non-trivial ADR, during the index hospitalization, assessed at 14 days post-randomization or at index hospital discharge if it occurs earlier. Potential ADRs are identified retrospectively by the site researchers who complete a Potential Endpoint Form (one per type of event) that is adjudicated by a blinded, expert committee. All occurrences of 12 pre-specified events, which represent the majority of ADRs, are reported to the committee along with other suspected ADRs. Participants are followed up 12 (+/− 4) weeks post-index hospital discharge to assess medication quality and healthcare utilization.

This is the first clinical trial to examine the effectiveness of a software intervention on incident ADRs and associated healthcare costs during hospitalization in older people with multi-morbidity and polypharmacy.

**Trial registration number:**

Clinicaltrials.gov NCT02097654, 27 March 2014.

## Background

Adverse drug reactions (ADRs) represent a significant and growing global healthcare problem, especially in the elderly population. ADRs may both cause hospitalization, and/or occur in hospital. Approximately 11% of hospital admissions in adults aged ≥65 years are caused by ADRs [1], while one in ten hospitalised patients are reported to experience an ADR during their inpatient stay [2]. Older age [2], female gender [3], multi-morbidity [4], polypharmacy [4] and frailty [5] are significant predictors of ADRs and are central to the GerontoNet ADR prediction tool described in 2010 [6]. Since approximately half of all ADRs are thought to be preventable [7], they represent a major, modifiable contributor to morbidity and mortality in older subjects.

Inappropriate prescribing and excessive polypharmacy are both linked to ADRs, but few interventions addressing these risks have been evaluated. A recent single centre clinical trial showed that the application of the ‘Screening Tool of Older Persons’ Prescriptions’ (STOPP) and ‘Screening Tool to Alert doctors to the Right Treatment’ (START) screening tools by an experienced geriatrician within 48 h of admission reduced incident in-hospital ADRs from 21.0 to 11.7% [8]. Patients recruited to this study were adults 65 years and older admitted acutely to hospital; patients were excluded if they were admitted directly to the intensive care unit, under geriatric medicine, old age psychiatry, clinical pharmacology or palliative medicine. Additional studies have shown that the manual (i.e. not delivered by software) application of STOPP/START criteria improves medication appropriateness [9, 10] and reduces the risk of falls [11]. However, these trials have been single centre and unblinded. Furthermore, the lack of sufficient geriatric medicine specialists limits the applicability of this manual approach. To overcome these limitations, a novel software tool called SENATOR (Software ENgine for the Assessment and optimisation of drug and non-drug Therapy in Older peRsons) was developed, which automatically provides individualized STOPP/START and other relevant recommendations based on standardized inputs. Given the support in the literature for the efficacy of the STOPP/START recommendations, we decided to conduct a pragmatic trial to quantify the effectiveness of providing the individualised SENATOR software report to the participating patient’s attending hospital clinician for review and implementation as he/she judges appropriate compared to usual clinical care, with the aim of reducing in-hospital ADRs amongst older adults in a real world setting across 6 European hospitals.

## Methods

The SENATOR Trial is a multinational, pragmatic, parallel arm Prospective Randomized Open-label, Blinded Endpoint (PROBE) controlled trial [12]. It is pragmatic in nature, in that it aims to evaluate the SENATOR software in real world clinical practice with decisions being made by busy clinicians. The trial is funded by the European Union Framework Programme 7 and includes a diverse geographical make-up, with participation of six large university-affiliated hospitals from across Europe (Ireland, Scotland, Iceland, Spain, Italy and Belgium). The trial is registered with clinicaltrials.gov (NCT02097654).

### Entry criteria

To be eligible for inclusion, participants have to be 65 years or older and must be admitted to a hospital in a non-elective manner, under the care of a medical or surgical service, and have an initial management plan in place (Table 1). Subjects are required to have 3 or more active co-morbidities, defined as conditions requiring ongoing medical therapy. Patients are excluded if they are admitted under the care of specialists in geriatric medicine or clinical pharmacology, or if they have already been reviewed by these services or are scheduled to undergo such a consultation, since these services provide similar advice to the SENATOR software, potentially supressing the observed ADR event rates and making it more difficult to detect any benefit from the intervention. Similarly, patients admitted to intensive care units or under the care of oncologists, as well as patients with liver failure, renal failure receiving dialysis, and patients with solid organ transplants, will also be excluded, since detailed specialist scrutiny and adjustment of prescribed medications occur regularly in these settings. As ADR rates are highest in the initial days following admission, patients are required to give their informed consent within 48 h of arrival to hospital and be randomized within 60 h of arrival. To allow for adequate follow-up, subjects are excluded if the anticipated length of their hospital stay is less than 48 h, if there is an existing documented intention to transfer them to another hospital, or if the attending clinician believes the subject’s life expectancy is less than 3 months.

**Table 1 Tab1:** SENATOR Trial: Inclusion and exclusion criteria

Inclusion criteria	
• ≥ 65 years • Admitted with an acute illness under the care of a specialist other than a geriatrician OR clinical pharmacologist OR palliative care physician OR oncologist OR haematologist • Consented into the study ≤60 h from time of arrival to the hospital • Anticipated in hospital stay of > 48 h, in the opinion of the treating physician • ≥ 3 active (requiring current medication) chronic medical disorders	
Exclusion criteria	
• Elective hospitalisation • Patients actively participating in another clinical trial of a medicinal product • Documented plan for consultation with Geriatric Medicine, Clinical Pharmacology, Palliative Medicine, Clinical Oncology or Haematology specialist services at the time of study recruitment • Admission directly to an intensive care unit • Primary acute psychiatric illness (excluding delirium) • Admission with non-accidental overdose/self-harm • Patients still under the care and responsibility of Emergency Department Physicians • Patients considered by the attending clinician to have a life expectancy of < 3 months • Anticipated immediate transfer to alternative non-participating clinical service/hospital • Receiving renal dialysis • Clinical diagnosis of acute liver failure • Solid organ transplant recipient • Admitted to hospital > 60 h at time of attempted randomization.	

### Intervention

The SENATOR software was designed by the project consortium and implemented by the Clanwilliam Group®. It produces a report, in the clinician’s native language, that identifies potential risks, and opportunities for improvement, in the participants’ current medication list. The report has 5 components: [1] recommendations for modifying or discontinuing a current medication; [2] recommendations to initiate a new medication (both based on the published STOPP/START guidelines); [3] identification of major drug-drug and [4] drug-disease interactions (both based on SafeScript®software and other local drug-drug and drug-disease interaction databases) [5] and non-pharmacological recommendations considered complementary to patients’ drug therapy. STOPP/START is a widely used series of heuristic rules aimed at optimizing drug prescribing in older patients [13], which has been validated in a range of settings. SafeScript® is a validated software system which uses the Summary of Product Characteristics (SPCs) of ATC coded medications in conjunction with ICD-10 coded conditions that was developed in the UK [14]. The non-pharmacological recommendations in the SENATOR report were based on the ‘**O**ptimal evidence-based **N**on-drug **T**herapies in **O**lder **P**eople’ (ONTOP) programme [15]; these evidence-based recommendations were developed independent of the trial as part of the same FP7 funded project. Only the ONTOP recommendations aimed at reducing the occurrence of incident delirium were completed and available for inclusion in the SENATOR report version used within the current trial. Since all older subjects who are hospitalized are at risk for developing delirium, the recommendations are provided to all subjects randomized to the SENATOR intervention, except those who already have delirium at the time of recruitment. The ONTOP recommendations are included by way of a demonstration of the potential utility of SENATOR as a potential mechanism for promoting non-pharmacological therapies i.e. as a proof of concept. However, the study was not powered with the aim of estimating the benefits of the ONTOP component.

In the intervention arm the participant’s clinical team receive an individualized SENATOR report, at a single time point within 60 h of hospital admission. Control arm subjects and their doctors receive no additional study specified intervention. All subjects have usual clinical management whereby as part of routine care clinicians routinely review and adjust medications according to their local practice. In addition, in one site the majority of hospitalized patients undergo a routine review of their medications by a dedicated internal liaison team or by a hospital pharmacist.

As SENATOR is a decision support tool, it efficiently provides in a single report a range of evidence based recommendations, derived from general considerations. Given the multiple complexities of clinical care, none of these recommendations is mandated. Rather clinicians are requested to review them in the context of the patient’s unique clinical circumstances and to make any alterations in accordance with the clinician’s best judgement.

### Randomization

The patients are randomized into one of the two trial arms with a 1:1 allocation ratio. Randomization is stratified by study site and by admitting service type (i.e. medical vs. surgical). The stratum-specific randomization lists are generated using random block sizes by an independent statistician.

### Allocation concealment

Trial allocation is delivered using an interactive Web-Response System developed in conjunction with the main trial database by Clininfo®, the data management partner company within the SENATOR project. Subject allocation is released once all necessary baseline information data have been entered into the trial database and a decision is made to randomize. In subjects randomized to the active intervention, trial data are automatically transferred to the cloud based SENATOR software engine maintained by Clanwilliam Health®, and the resulting SENATOR report is automatically emailed to the local trial research staff at a designated email.

### Report dissemination

The local research team members place a printed copy of the SENATOR report in the medical record or in the case of two sites that exclusively use an electronic patient record, uploads it electronically. The researcher further contacts a member of the clinical team and emails the attending physician alerting him/her of the report’s existence and requesting the attending physician to review it and consider its recommendations. No specific measures are applied to otherwise encourage or oblige the clinician to adopt any of the report’s recommendations. Given the nature of the intervention it is not possible to effectively mask the intervention from the clinical team or from the on-site researchers.

### Trial administrative structures

The trial is coordinated by a dedicated Trial Coordination Committee based in the Health Research Board (HRB) Clinical Research Facility at University College Cork. A Trial Steering Committee, comprising of the SENATOR grant work package leaders, meets regularly by teleconference and supervises progress and communication including protocol amendments. An independent seven member Scientific Advisory Board meet annually and review overall trial progress. The Scientific Advisory Board members are all senior academic clinicians, including five geriatricians, one clinical pharmacologist and one pharmacist. An independent Ethics and Data Safety Committee consisted of an academic geriatrician, a senior hospital internal medicine physician with an interest in ethics, a medical ethicist, and a patient advocate. The committee meets annually to review trial metrics and any potential trial related deleterious events. Trial Deleterious Events are also assessed by the Trial coordinating Committee in real time.

### Trial staff

The Trial Coordinating Committee is staffed by a dedicated Trial Manager, an Endpoint Liaison Officer (both full time) and a Data Manager, Biostatistician, and Trial Monitor (part-time) who are supervised by the Trial Coordinating Investigator. Each of the six sites is led by a site Principal Investigator (PI), who is a senior physician specializing in geriatric medicine and with extensive experience in geriatric pharmacotherapy. These PIs oversee the recruitment, training and conduct of the local trial staff. All site staff are ICH GCP certified researchers with medical, nursing or health science backgrounds. Training consists of live interactive tutorials, online ICD-10 training, case-based ADR adjudications, remote testing of the electronic case report form (eCRF) at each clinical site, a central two day and subsequent one day meeting of all local site staff and web-based site initiation visits prior to recruitment initiation. Audits were performed by the Clinical Research Facility in Cork (CRF-C) monitoring staff who were otherwise independent of the running of the trial.

### Data management

Although pragmatic and using a ‘real world’ approach to the dissemination of the SENATOR report and with a variable degree of engagement by the clinician, it has been necessary to develop and use a trial specific database to gather the inputs used by the SENATOR software in a standardized fashion from the different countries and to collect the trial outcome data which are collected to a far greater degree of precision and accuracy than is usual in clinical practise. To this end, data are entered electronically by the local site research staff into a cloud based database developed by Clininfo®. Data collected is pseudo-anonymized and includes baseline past medical history, current prescription medications and doses, routine blood biochemistry and haematology laboratory data, baseline ECG data, cognitive assessment using the Mini-Mental State Examination [16], functional assessment using the Barthel Index [17], and health related quality of life using the EQ-5D-5 L [18]. At day 14 post randomization or at discharge, whichever occurs first, the EQ-5D-5 L is repeated, the subjects medical conditions reviewed and medications recorded. The case records are reviewed to assess the number of SENATOR recommendations that have been adopted and to identify any potential endpoints as discussed below. At discharge arrangements are made with participants and/or their family for a 12 weeks (+/− 4 weeks) post hospital discharge follow-up call by the local site research staff. This is to enquire about healthcare utilization and any re-hospitalization since the index hospitalization, changes in medications and current health related quality of life.

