### Endpoint ascertainment

Potential ADRs are recorded by the site staff using dedicated primary endpoint assessment forms based on a retrospective review of all the available documentation within the medical record, including medical, nursing and allied health professional case note entries, laboratory values, radiology reports, electrocardiograms and other investigations. The eligible period for endpoint occurrence extends from the day of randomization to the time of index hospital discharge, or until 14 days post randomization, whichever occurs first. In those subjects whose discharge takes place after day 14 the medical record is further reviewed at the time of discharge to determine if any additional evidence from the subsequent hospital course is relevant to the aetiology of a potential study endpoint.

We identified the 12 most common types of ADRs which represent approximately 80% of all hospital-acquired ADRs in older multimorbid patients (Table 2). For each of these pre-specified types of event, we developed a separate primary endpoint event-specific form, based on a standard template as shown in Fig. 1, to allow for standardised ascertainment of data relevant to that type of event. Any other type of suspected ADRs is recorded using a generic primary endpoint adverse event form. As several medications may be implicated in the same event, the most likely culprit medication, if identifiable, and any other potentially causal or contributory medications implicated in the adverse event are recorded. Generic evidence that supports causality such as temporal relationship, dose response relationship, and response to re-challenge, are recorded, along with any additional qualifying explanatory text used by the local research staff. The unblinded Site Investigator records whether the ADR began prior to randomization (i.e. was prevalent and therefore not part of the primary endpoint) or occurred post-randomization, and his/her own assessment as to the probability of the event being an ADR, and the severity of the event. The strength of the available evidence supporting the event being an ADR is ascertained using the WHO-UMC ADR causality classification system [19], which categorizes ADRs as certain, probable, possible, unlikely or indeterminate. The severity of the event is classified using a modified Hartwig & Siegel scale [20], ranging from trivial (event requires no specific investigation or treatment and has no sequellae) to fatal.

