**Fig. 1 Fig1:**
[figure not shown]
Potential Endpoint Adjudication Process

While the recording of evidence supporting an ADR, in a blinded fashion, using the relevant Potential Endpoint Form facilitates the blinded assessment of possible ADRs by the Adjudication Committee, it does not in itself safeguard against the possibility of selective or differential reporting of events to the Adjudication Committee by local site staff. This is especially relevant in the context of an open label trial, as the decision to refer borderline events/possible ADRs is often highly subjective. To avoid against the incomplete or differential submission of potential endpoints according to study arm, we have mandated that all occurrences of the 12 pre-specified events as listed on Table 2 be reported regardless of their presumed aetiology. Compliance with this reporting approach is assessed by on-site monitoring.

Given the difficulty with objectively and reliably recording the number of separate discrete occurrences of a specific type of ADR (e.g. episodes of diarrhoea), especially when using retrospective data review, we have taken the approach of completing a single Potential Endpoint Form for each type of ADR. This summarizes the total available evidence that a particular drug played an etiological role in the genesis of part or the totality of the adverse event that may represent an ADR. Thus, only one form is completed for each type of event regardless of the number of possible discrete occurrences of that particular adverse event during the index hospitalization. A subject could experience several different types of ADRs which are each recorded on their specific case report form or on the generic Potential Endpoint Form, as appropriate.

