### Sample size

In a recent single blinded trial of the manual application of STOPP/START criteria, conducted at the coordinating investigator site, the observed control group hospital-acquired ADR incidence was 21% compared to an ADR incidence of 11.5% in the intervention group, equivalent to an ADR odds-ratio of 0.45 [8]. This study had similar entry criteria and primary endpoints to the current trial, but differed in that the STOPP/ START recommendations were manually generated and then directly discussed and reviewed with the primary team by a specialist registrar (senior resident) in geriatric medicine. To be conservative, and in view of the more rigorous ADR adjudication processes, we have based our power calculations for the current trial on a lower control group event rate (18%) than that seen in our earlier trial, and we assume a reduced effect size (an odds ratio of 0.65) in order to reflect the potential reduced uptake of recommendations by clinicians. Based on these assumptions, using the method of Farrington and Manning for a trial to test the difference between two binomial events with a two-sided type 1 error rate of 0.05, we achieve 90% power with the proposed recruitment of 900 subjects per trial arm. The planned CONSORT flow diagram for the trial is shown in Fig. 3.

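### The primary endpoint is open to differential ascertainment by arm: unmasked staff find endpoints in the review that also scores adoption of the SENATOR report, and the safeguard covers only the 12 listed event types

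*Protocol article*

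**What the plan says.** All references are to the protocol article.

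- **Data management.** The review at day 14 or discharge has two tasks: "The case records are reviewed to assess the number of SENATOR recommendations that have been adopted and to identify any potential endpoints".
- **Allocation concealment and Report dissemination.** For intervention patients only, the software report is emailed to the local research staff. They then "place a printed copy of the SENATOR report in the medical record" (two sites upload it electronically) and alert the clinical team. The article states that on-site researchers cannot effectively be masked.
- **Endpoint ascertainment.** Site staff complete the forms from a retrospective review of the medical record. Twelve event types have their own forms, "which represent approximately 80% of all hospital-acquired ADRs in older multimorbid patients". For the rest, "Any other type of suspected ADRs is recorded using a generic primary endpoint adverse event form".
- **Endpoint ascertainment, text after Fig. 1.** The article accepts that blinded adjudication does not prevent selective referral, noting that "the decision to refer borderline events/possible ADRs is often highly subjective". Its answer is to require every occurrence of the 12 listed events to be reported whatever the cause, with on-site monitoring of compliance.
- **Trial endpoints and Secondary endpoints.** The primary endpoint takes any adjudicated probable or certain, non-trivial incident ADR, listed or not. Two secondary endpoints, one a proportion and one a count, are limited to the listed types.

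**The concern.** Scoring adoption means going through the report's list of drugs to stop, interactions and drug-disease risks, and noting which advice was followed. That task exists in one arm only. If the same person is also deciding which events look drug-related, the intervention arm has a prompt that the control arm lacks.

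The prompt could act either way. A list of hazards may raise suspicion in the intervention arm and mask a real benefit. Knowing that the advice was followed may lower suspicion and produce an apparent benefit.

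Mandatory reporting closes this route for the 12 listed types, but the article describes no comparable safeguard for the others. Blinded adjudication cannot recover an event that was never referred. The exposure also reaches listed events to some degree, because site staff write the suspected culprit drug and the causality evidence on every form, and the unblinded investigator records whether onset preceded randomization.

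**Working it through.** **Inputs from the Sample size section.** Control rate 18%, odds ratio 0.65, "two-sided type 1 error rate of 0.05", and "we achieve 90% power with the proposed recruitment of 900 subjects per trial arm".

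**Step 1: reproduce the design.** Intervention odds = 0.65 × 0.18/0.82 = 0.1427, so the intervention rate is 0.1427/1.1427 = 12.49%. A two-sided comparison of 18% with 12.49%, using the normal approximation with pooled variance under the null, needs 892 per arm for 90% power and gives 90.3% power at 900 per arm. The stated figure is reproduced.

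**Step 2: the share resting on suspicion.** From Endpoint ascertainment, 100% − 80% = about 20% of ADRs. This counts ADRs, not patients. A patient who also has a qualifying listed ADR is an endpoint in any case, so the share s of endpoint patients who qualify only through a non-listed ADR may be below 20%. I use s = 20% and s = 10%.

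**Step 3: model differential referral.** Let m be the relative difference in referral of non-listed ADRs in the intervention arm compared with control. The article gives no value; 25% and 50% are assumptions. The control rate stays at 18%.

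- Observed intervention rate = true rate × (1 + s × m)
- Observed odds ratio = [p/(1 − p)] / [0.18/0.82]
- Rejection probability: the test of step 1 with 900 per arm, both tails

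| Truth | s | m | Intervention rate | Observed OR | Rejection |
|---|---|---|---|---|---|
| OR 0.65 | 20% | +25% | 0.1249 × 1.05 = 13.11% | 0.69 | 82% |
| OR 0.65 | 20% | +50% | 0.1249 × 1.10 = 13.74% | 0.73 | 70% |
| No effect | 20% | −25% | 0.18 × 0.95 = 17.1% | 0.94 | 7.9% |
| No effect | 20% | −50% | 0.18 × 0.90 = 16.2% | 0.88 | 17% |
| OR 0.65 | 10% | +25% | 0.1249 × 1.025 = 12.80% | 0.67 | 86% |
| No effect | 10% | −25% | 0.18 × 0.975 = 17.55% | 0.97 | 5.7% |

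**Step 4: an upper limit for this route.** With s = 20% and no non-listed ADR referred at all in the intervention arm (m = −100%), the rate is 0.18 × 0.80 = 14.4% and the odds ratio under no effect is 0.77. At that share, this route alone would not produce the design value of 0.65.

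**The case against.** A reader might infer that the endpoint is in fact ascertained differently in the two arms. The article does not support that. It shows opportunity, not occurrence, and does not say that one person does both tasks at one sitting or in what order. An article may also leave form order to a full protocol or site manual.

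Other points against the concern have weight:

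- The trial recognises the risk. It mandates reporting for most ADRs, monitors compliance, uses adjudicators from other sites and has secondary endpoints limited to listed events.
- The article's remark on subjectivity concerns borderline and possible ADRs, whereas the primary endpoint needs probable or certain ones. The examples given for unlisted events, acute liver failure and anaphylaxis, are unlikely to go unsuspected.
- The 25% and 50% differences have no source in the article. They describe any differential referral in an open-label trial, not the increment from combining the two tasks.
- Staff have handled the report before the review, so reordering the tasks cannot undo what they know.

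These points limit the size and certainty of the concern. They do not remove it: the article itself joins the two tasks, and its stated remedy stops at the listed types while the primary endpoint does not.

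**Conclusion.** The point holds as a vulnerability in the design. The primary endpoint is open to differential ascertainment by arm, and the article describes no safeguard for ADRs outside the 12 listed types. The direction is unknown, so the analysis cannot correct for it.

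The size rests on two assumptions, the share s and the referral difference m. With a 20% share, differences of 25% to 50% cost about 8 to 20 points of power, or raise two-sided rejection under no effect from 5% to about 8% to 17%. With a 10% share and a 25% difference the effect is slight. Reading 20% as the share of endpoint patients would go beyond the article, which gives a share of ADRs. The point therefore supports an inexpensive improvement, not a change of endpoint or sample size.

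**What to change.** In Data management and Endpoint ascertainment, state the order of work:

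1. The endpoint search is completed from the clinical record with the SENATOR report left unopened. All Potential Endpoint Forms, including the generic form, are then submitted and locked.
2. Only then does the eCRF open the page for scoring adoption of recommendations.
3. For stays beyond day 14, later evidence is added as a dated addendum and the locked entries stay unchanged.

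Report generic-form referrals per patient by arm, before adjudication, and read the existing listed-events secondary endpoint beside the primary result as a check.

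The cost is one eCRF sequencing rule, a line in the site manual and one table; no extra staff are needed. The downside is a two-step record review. Staff who remember the allocation or the report remain unblinded, so the bias is reduced, not removed.
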